#### Primary Objectives

##### Objective 1

The first objective aims to answer: Does a program for psychosocial assessment during pregnancy influence the prevalence of pregnant women receiving psychological or medical treatment for mental ill-health?

##### Objective 2

The second objective aims to answer: Does a program for psychosocial assessment during pregnancy influence the time point for identification of mental ill-health in pregnant women?

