#### Measurements

Objective 1 includes data from the SPR, which will be compared pre- and postimplementation of the program for psychosocial assessment, and captures the prevalence of patients who have received (1) medical treatment prepregnancy or during pregnancy, (2) psychological treatment for mental ill-health prepregnancy or during pregnancy, and (3) both medical and psychological treatment prepregnancy or during pregnancy.

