#### Statistical Analysis

Logistic regression analysis, including an indicator variable for pre- and postimplementation, will be performed. The model will also include variables to adjust for potential confounding variables (eg, age, primiparous women, civil status, employment status, maternity clinic), selected according to the disjunctive cause criterion [38].

The effect measure will be the odds ratio (OR) with 95% CIs.

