#### Statistical Power

Based on data from the SPR, which recorded 8246 births between 2017 and 2019 and 7611 births between 2021 and 2023, and an initial prevalence of identified cases of mental ill-health of 7%, the MDD for this register-based study was calculated. Using a 2-sided 2-sample *z* test for proportions with a 5% significance level (α=.05) and 80% power, the MDD was estimated at 0.8%. This indicates that the study will be capable of detecting changes of 0.8 percentage points or greater, thereby ensuring sufficient sensitivity to identify any clinically meaningful differences.

### Objective 2

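### The outcome of primary Objective 1 is not fixed: the question is about psychological or medical treatment, but the listed measures are medical, psychological and both, with no either-treatment outcome

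*Protocol article*

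**What the plan says.** Under Primary Objectives, the protocol article asks whether the program will "influence the prevalence of pregnant women receiving psychological or medical treatment for mental ill-health".

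Under Objective 1, Measurements, it lists three prevalences to compare before and after implementation. The first is "1) medical treatment prepregnancy or during pregnancy". The second is the corresponding measure for psychological care, with the same time window. The last on the list is "3) both medical and psychological treatment prepregnancy or during pregnancy". None is marked as the main one.

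Under Objective 1, Statistical Analysis, "Logistic regression analysis, including an indicator variable for pre- and postimplementation, will be performed", and "The effect measure will be the odds ratio (OR) with 95% CIs". The dependent variable is not named.

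Under Objective 1, Statistical Power, the register "recorded 8246 births between 2017 and 2019 and 7611 births between 2021 and 2023", and the calculation takes "an initial prevalence of identified cases of mental ill-health of 7" per cent, giving a stated minimum detectable difference of 0.8 percentage points.

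**The concern.** Read plainly, the objective concerns one group: women with at least one of the two treatments. The list contains each treatment and their intersection, but not their union. Question, measures, model and power basis therefore do not share one stated outcome.

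The text also leaves open whether a woman with both treatments counts once, under the third measure only, or under all three. This matters because the program adds psychologist consultation, funding for psychological treatment and referral pathways. Some women already on medical treatment may well gain psychological treatment. If the categories are exclusive, such a woman leaves the medical category and enters the combined one, so added care appears as a fall in medical treatment.

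At stake is whether the report on the first primary objective gives the effect that the objective asks about, and whether readers can tell what a change in each listed measure means.

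**Working it through.** **Sections side by side (all under Objective 1 except the first)**

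| Section | Outcome as stated |
|---|---|
| Primary Objectives | psychological or medical treatment |
| Measurements | medical; psychological; both |
| Statistical Analysis | not named |
| Statistical Power | identified cases of mental ill-health, 7% |

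**What can be derived.** Write M, P and B for the prevalences of medical, psychological and both, and U for either treatment. If M and P include B, then U = M + P − B. If the categories are exclusive, U = M + P + B. The crude union is available once the rule is known. The planned measure is an adjusted odds ratio, and the adjusted odds ratio for U with its confidence interval does not follow from three separate models for M, P and B. It needs a model of its own.

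**The plan's power figure.** Inputs from Statistical Power: 8246 and 7611 births, 7% baseline, two-sided 5%, 80% power. Solving the two-sample z test for an increase gives 1.18 points. Check at 7% to 8.18%:
- pooled p = (8246×0.07 + 7611×0.0818)/15857 = 0.0757
- SE under the null = √[0.0757×0.9243×(1/8246 + 1/7611)] = 0.00420
- SE under the alternative = √[0.07×0.93/8246 + 0.0818×0.9182/7611] = 0.00421
- 1.96×0.00420 + 0.842×0.00421 = 0.0118

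For a decrease the result is 1.09 points. The stated 0.8 corresponds to about 50% power (0.815 up, 0.775 down). This discrepancy is a separate matter. It is relevant here only because the power statement has to be restated for the chosen outcome. If either treatment has a baseline between 3% and 14% (assumed range), the detectable increase runs from 0.81 to 1.58 points.

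**Illustration 1: the counting rule.** All prevalences are assumed.

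| | Before | After |
|---|---|---|
| Medical only | 4% | 3% |
| Psychological only | 2% | 3.5% |
| Both | 1% | 3.5% |
| Either (sum) | 7% | 10% |

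- Either: (0.10/0.90)/(0.07/0.93) = 1.48.
- Medical, exclusive: (0.03/0.97)/(0.04/0.96) = 0.74. SE of the difference = √(0.04×0.96/8246 + 0.03×0.97/7611) = 0.0029, so z is about −3.4.
- Medical, overlapping: 4+1 = 5% to 3+3.5 = 6.5%, and (0.065/0.935)/(0.05/0.95) = 1.32.

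The women are the same, but the direction for medical treatment is opposite.

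**Illustration 2: overlapping categories, union unchanged.** All prevalences are assumed.

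| Measure | Before | After | OR | z |
|---|---|---|---|---|
| Medical | 4.5% | 3.5% | 0.77 | −3.2 |
| Psychological | 4.0% | 5.5% | 1.40 | 4.5 |
| Both | 1.5% | 2.0% | 1.34 | 2.4 |
| Either | 4.5+4.0−1.5 = 7.0% | 3.5+5.5−2.0 = 7.0% | 1.00 | 0 |

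For the first row, (0.035/0.965)/(0.045/0.955) = 0.77. The pooled p is 0.0402, the SE is 0.00312, and −0.01/0.00312 = −3.2. All three listed measures move beyond 1.96 standard errors while the union does not change.

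**The case against.** The strongest reply is that psychological or medical can be read as two questions, one per treatment type. Measures (1) and (2) answer those directly. The Measurements section describes what the register captures and does not rule out a combined analysis. The Background already cites a register figure for women treated for mental ill-health without splitting by type (11% nationally in 2023). The analysis section speaks of one model and one odds ratio, which would fit a single combined outcome. The wording is medical treatment, not medical only, so overlap is the more natural reading. On that reading the reclassification effect in Illustration 1 disappears, and the fall in medical treatment in Illustration 2 is a real fall. Much of this stands, and it rules out saying that nothing in the list bears on the objective.

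Two things remain. On the two-question reading, the text still does not say which outcome the model uses, and the power basis is still neither of the two. On the one-question reading, the planned adjusted effect for either treatment is not provided for. A condensed article may leave detail to a fuller document, but here the article states its list of measures and the list does not match the stated question. For secondary Objective 3 it does name a main focus (referrals to psychological treatment).

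A reader might also infer uncontrolled multiplicity across three outcomes. The documents do not support that. No rule declares success on any one outcome, the measures are dependent (nested if they overlap), and ranking rules may stand in a plan that is not shown.

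**Conclusion.** The point holds as a mismatch between the primary question and its stated measures. The either-treatment outcome is not listed, the relation of measures (1) and (2) to (3) is not stated, the model has no named dependent variable, and the power figure rests on a differently labelled prevalence.

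It would go too far to conclude that no outcome answers Objective 1. Measures (1) and (2) answer part of it, and the crude union can be derived. What is missing is the adjusted odds ratio for either treatment.

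The actual size cannot be given, because the document reports no prevalence by treatment type. The illustrations show only what is possible. The odds ratio of 0.74 needs the exclusive reading and assumed levels, and applying 7% and 10% to any treatment is itself an assumption, since the article uses those figures for identified mental ill-health. The matter should be settled before the extraction planned for 2025-2026.

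**What to change.** - **Measurements:** name any treatment for mental ill-health (medical, psychological or both) as the primary outcome of Objective 1. List medical (with or without psychological), psychological (with or without medical) and both as secondary components, and state that they overlap.
- **Statistical Analysis:** name the primary outcome as the dependent variable of the logistic model.
- **Statistical Power:** base the statement on the prevalence of that outcome. If 7% is taken to apply to it, say so and recompute the detectable difference (1.18 points for an increase, as shown above).

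**Cost:** a few sentences and one recalculation, plus one practical condition. The Sample Size Calculation section describes the register data as anonymous and aggregated. The extract must therefore be individual-level, or cross-tabulated so that the either-treatment variable can be formed together with the covariates. If it is ordered as three separate totals, the adjusted analysis of the primary outcome cannot be done.

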#### Statistical Analysis

Logistic regression analysis, including an indicator variable for pre- and postimplementation, will be performed. The model will also include variables to adjust for potential confounding variables (eg, age, primiparous women, civil status, employment status, maternity clinic), selected according to the disjunctive cause criterion [38].

The effect measure will be the odds ratio (OR) with 95% CIs.

#### Statistical Power

Based on data from the SPR, which recorded 8246 births between 2017 and 2019 and 7611 births between 2021 and 2023, and an initial prevalence of identified cases of mental ill-health of 7%, the MDD for this register-based study was calculated. Using a 2-sided 2-sample *z* test for proportions with a 5% significance level (α=.05) and 80% power, the MDD was estimated at 0.8%. This indicates that the study will be capable of detecting changes of 0.8 percentage points or greater, thereby ensuring sufficient sensitivity to identify any clinically meaningful differences.

### Objective 2

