### Estimated Sample Size and Power

#### Sample Size Calculation

Calculation of the sample size was initially based on objective 1, using Minitab 16. The calculation was based on data from the SPR 2017 with a 7% initial prevalence of mental ill-health among pregnant women in the Västmanland Region [37], with an expected increase to 10% due to the rise in detection attributable to the program’s implementation. In order to detect an increase by 3 percentage points in identified mental ill-health, with 80% power and a significance level of 5% (2-sided test), at least 534 pregnant women had to be included in each group. The inclusion of several different maternity clinics in the project was also taken into consideration, and we estimated a dropout rate of approximately 20%. This meant that 640 pregnant women had to be included in each group for both pre- and postimplementation measurements.

However, the emergence of the COVID-19 pandemic introduced unforeseen challenges, particularly with regard to participant recruitment and data representativeness. It was hypothesized that the pandemic may have influenced the prevalence of mental ill-health in the target population, potentially confounding the original pre-post comparisons.

In response, a revised strategy for objective 1 was implemented. A new ethical approval was obtained to extend data inclusion and allow for the anonymous use of aggregated register data from the SPR, covering all pregnant women in the Västmanland Region during 2017-2019 (preimplementation) and 2021-2023 (postimplementation). This adjustment enabled a substantial increase in sample size and improved the generalizability of findings for objective 1 while minimizing selection bias and increasing statistical power.

Importantly, although the revised strategy for objective 1 now relies on registry-based data with a broader population base, the original sample size calculations remain valid for objectives 2-4, which continue to use the survey-based data set from pre- and postimplementation phases. The sample size for these objectives was not altered, and the statistical power for each is described in general terms in the following paragraphs.

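### Objective 1 analyses treatment received, but its detectable difference is stated for identified mental ill-health at one 7% baseline, and the 0.8-point figure does not follow from its own inputs

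*Protocol article*

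**What the plan says.** Under Primary Objectives, Objective 1 asks whether the program will "influence the prevalence of pregnant women receiving psychological or medical treatment for mental ill-health". The Measurements section for Objective 1 names the register data that "captures the prevalence of patients who have received (1) medical treatment prepregnancy or during pregnancy", followed by psychological treatment and by both together. The analysed outcomes are therefore three prevalences of treatment received.

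The planning figures use another term. In the Sample Size Calculation section, "Calculation of the sample size was initially based on objective 1, using Minitab 16", and the target is set as follows: "In order to detect an increase by 3 percentage points in identified mental ill-health". The expected move from 7% to 10% is attributed there to better detection. That calculation was later replaced for Objective 1 by a register-based strategy.

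The current statement is in the Statistical Power section of Objective 1. It uses register data "which recorded 8246 births between 2017 and 2019 and 7611 births between 2021 and 2023", together with "an initial prevalence of identified cases of mental ill-health of 7" per cent, and a two-sided two-sample z test "with a 5% significance level (α=.05) and 80% power". It reports a minimum detectable difference of 0.8% and infers that "the study will be capable of detecting changes of 0.8 percentage points or greater". It adds that this is sensitive enough for any difference of clinical importance.

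**The concern.** Identification and treatment are separate steps in this article. Objective 2 is about when mental ill-health is identified. Objective 3 is about what is done once it has been identified, including treatment and referral. A detectable difference stated for identified cases does not automatically describe treatment received.

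The detectable difference also depends on the baseline rate, and three outcomes will in general have three baselines. If the first two categories include women who had both treatments, the third cannot be more common than either of them. One 7% figure cannot stand for all three.

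What is at stake is how a null or small result is read. Objective 1 is a primary objective, and its power section offers a strong assurance of sensitivity. If that assurance rests on a mislabelled outcome and a figure that is too small, a non-significant change of around one percentage point could be reported as evidence that nothing clinically important happened, when the comparison could easily have missed it.

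**Working it through.** **Inputs** (Objective 1, Statistical Power): n1 = 8246, n2 = 7611, p1 = 0.07, two-sided α = 0.05 (z = 1.960), power 80% (z = 0.842), two-sample z test for proportions.

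**Step 1: reproduce the stated 0.8 points.** With the baseline variance in both groups:

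MDD = (1.960 + 0.842) × √[p1(1 − p1)(1/n1 + 1/n2)]

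- p1(1 − p1) = 0.07 × 0.93 = 0.0651
- 1/8246 + 1/7611 = 0.00025266
- standard error = √(0.0651 × 0.00025266) = 0.004056
- MDD = 2.802 × 0.004056 = 0.01136, or **1.14 points**

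With the pooled variance under the null and separate variances under the alternative, solving for 80% power gives **1.18 points** for an increase and **1.09 points** for a decrease. A one-sided test still gives 1.01 to 1.04. The stated 0.8 is not reproduced.

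**Step 2: power for 7.0% against 7.8%.**

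- pooled rate = 0.07 + 0.008 × 7611/15857 = 0.07384
- null standard error = √(0.07384 × 0.92616 × 0.00025266) = 0.004157
- alternative standard error = √(0.0651/8246 + 0.071916/7611) = 0.004165
- power = Φ[(0.008 − 1.960 × 0.004157)/0.004165] = Φ(−0.035) = **49%**

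**Step 3: where 0.8 might come from.** Values near 0.8 appear only with formulas that do not fit a two-group comparison at 80% power:

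- one-sample formula: 2.802 × √(0.0651/8246) = 0.79 points, or 0.82 with 7611
- total of 15,857 used as the size of each group: 2.802 × √(0.0651 × 2/15857) = 0.80 points
- power term left out: 1.960 × 0.004056 = 0.79 points

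The article does not show which, if any, was used.

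**Step 4: detectable difference at other baselines.** The article gives no regional pre-implementation rate for any treatment outcome, so the baselines below are assumptions. Group sizes, α and power are as above (pooled null variance).

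| Baseline | Detectable increase (points) | Detectable decrease (points) | Power for +0.8 points |
|---|---|---|---|
| 2% | 0.672 | 0.578 | 91% |
| 3% | 0.807 | 0.715 | 79% |
| 5% | 1.015 | 0.927 | 61% |
| 7% | 1.179 | 1.095 | 49% |
| 11% | 1.431 | 1.355 | 35% |

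The 11% row uses the only treated share from this register in the article (Background: national, 2023). It is neither regional nor pre-implementation. The 0.8-point claim for an increase holds only at baselines of about 3% or lower.

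**The case against.** The strongest reply is that the mismatch is only one of wording. The 7% is attributed to the pregnancy register for 2017, and the only mental-health quantities the article attributes to that register are treatment figures: the 11% treated in the Background and the measures for Objective 1. Identification is to be read from medical records, under Objective 2. The 7% may therefore already be a treated rate. This stands as a possibility, and it rules out asserting that the baseline belongs to a different outcome. It does not settle the matter: both planning sections speak of identified cases, and the earlier one justifies the rise by detection. Even if the label is the only slip, the sections need reconciling, and one rate still does not describe three outcomes.

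A second reply is that a condensed article may give one representative baseline and leave the rest to the full protocol. That is fair as far as omission goes. But this article states a figure and draws a broad conclusion from it, and the figure is wrong for the baseline it names.

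A reader might go further and infer that, since only some newly identified women start treatment, a 3-point detection gain would produce a treatment change too small to find. The documents do not support that. The 3-point effect belongs to the calculation that the register strategy replaced, and the current power section assumes no effect size. No share of newly identified women starting treatment is given. The Implementation Strategies section also describes added funding for psychological treatment and clearer referral pathways, which could raise treatment among women who were already identified. No power figure should be built on that chain.

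**Conclusion.** The point holds in two parts. First, the stated sensitivity is not shown for any outcome that Objective 1 will analyse, because its baseline is labelled as identified cases and no rate is given for medical, psychological or combined treatment. Whether the 7% is truly an identified rate cannot be decided from the article.

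Second, and larger in effect, the 0.8 points is wrong for the 7% baseline whatever that rate measures. It should be about 1.2 points for an increase or 1.1 for a decrease. This part needs no assumption beyond the article's own inputs.

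Baseline choice alone moves the detectable increase from 1.18 at 7% to 1.43 at 11%, or down to 0.81 at 3% and 0.67 at 2%. The rarest treatment outcome could therefore meet the stated figure, while more common ones would not. The register sample remains large. What fails is the stated figure and the blanket assurance drawn from it, not the feasibility of the comparison.

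**What to change.** In the Statistical Power section of Objective 1:

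1. State whether the 7% is a treated or an identified rate, and bring the wording into line with Primary Objectives, Sample Size Calculation and the Objective 1 Measurements section.
2. Replace 0.8 with the recomputed detectable difference for each of the three treatment outcomes, using its own 2017-2019 register rate, and name the formula and the direction of change. If 7% is kept as an illustration, the figure is about 1.2 points for an increase.
3. Delete the claim that any clinically important difference can be identified, or limit it to outcomes and differences for which the recomputed figures support it.

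The cost is recalculation and wording only; design, data and analysis model stay as they are. The stated figure becomes less favourable for most baselines. The article schedules Objective 1 data collection for 2025-2026, so the correction can be made before the results are compiled.

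### Objective 1's minimum detectable difference is about 1.2 percentage points on the stated inputs, not 0.8; power at 0.8 points is about 49%, not 80%

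*Protocol article*

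**What the plan says.** The Statistical Power section under Objective 1 sets out a complete calculation for the register comparison. The group sizes come from the Swedish Pregnancy Register, "which recorded 8246 births between 2017 and 2019 and 7611 births between 2021 and 2023", and the baseline is "an initial prevalence of identified cases of mental ill-health of 7" percent. The method is also given: "Using a 2-sided 2-sample *z* test for proportions with a 5% significance level (α=.05) and 80% power". The result is that "the MDD was estimated at 0.8%. This indicates that the study will be capable of detecting changes of 0.8 percentage points or greater". The same sentence ends by describing this as "ensuring sufficient sensitivity to identify any clinically meaningful differences".

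The MDD is printed first as a percentage and then as percentage points, so it is an absolute difference. The Sample Size Calculation section shows which direction is expected. It planned for a 7% starting prevalence "with an expected increase to 10% due to the rise in detection attributable to the program’s implementation".

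**The concern.** With about 8000 births per period and a 7% prevalence, the standard error of the difference is about 0.41 points. An 80%-power MDD at two-sided 5% is about 2.8 standard errors, which is well above 0.8 points. The printed value is close to 1.96 standard errors. That is the significance threshold, which a true difference of that size crosses only about half the time.

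This is the only current numerical power statement for the first primary objective. The calculation for 534 women per group was superseded for Objective 1 when the design moved to register data, and that move was justified partly by a gain in power. A reader of a non-significant result who relied on the printed figure would think a 0.8-point change had an 80% chance of being detected. The design would miss such a change about half the time.

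**Working it through.** **Inputs** (Objective 1, Statistical Power): n₁ = 8246, n₂ = 7611, p₁ = 0.07, two-sided α = 0.05 (z = 1.96), power 80% (z = 0.842).

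**Trying to reproduce 0.8.** Using the baseline variance only:

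- SE₀ = √[0.07 × 0.93 × (1/8246 + 1/7611)] = 0.004056
- (1.96 + 0.842) × SE₀ = 0.01136, or 1.14 points
- 1.96 × SE₀ = 0.00795, or 0.8 points

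The printed value appears when the power term is dropped. It does not appear at 80% power.

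**Power at the printed MDD, pooled z test.** Power = Φ[(|p₂ − p₁| − 1.96 × SE_null) / SE_alt]. SE_null uses the pooled proportion p̄. SE_alt = √[p₁(1 − p₁)/n₁ + p₂(1 − p₂)/n₂].

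- Increase, 7.0% to 7.8%: p̄ = 0.07384, SE_null = 0.004157, SE_alt = 0.004165. Power = Φ[(0.008 − 0.008147)/0.004165] = Φ(−0.035) = 48.6%.
- Decrease, 7.0% to 6.2%: SE_null = 0.003951, SE_alt = 0.003942. Power = Φ(0.065) = 52.6%.

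**MDD at 80% power.** Solving the same equation for the difference gives:

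- Increase: 0.01179, or 1.18 points (7.0% to 8.18%)
- Decrease: 0.01095, or 1.09 points

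Against the printed value, 1.18/0.8 = 1.47, so the MDD for an increase is about 47% larger than stated.

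**Other conventions, same inputs, 80% power:**

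| Method | Increase | Decrease |
|---|---|---|
| Pooled z, two-sided | 1.18 | 1.09 |
| Arcsine, two-sided | 1.18 | 1.09 |
| Baseline variance only, two-sided | 1.14 | 1.14 |
| Continuity-corrected, two-sided | about 1.19 | not solved |
| Pooled z, one-sided 5% | 1.04 | 0.98 |

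Unpooled variance gives power of 48.4% at +0.8 and 52.8% at −0.8. None of these gives 0.8 points at 80% power.

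**Sample needed for 0.8 points.** For 7.0% against 7.8% at 80% power, equal groups would need about 16,806 births each. At the protocol's own ratio the need is about 17,494 before and 16,150 after. Either is roughly twice what is available.

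**Check against the protocol's other MDDs.** The Dichotomous Outcomes section states 8, 5 and 4 points at prevalences of 50%, 10% and 5% for the survey sample of 487 and 942. The same pooled formula for an increase gives 7.8, 5.2 and 4.1 points. Those figures follow the standard 80%-power calculation; the Objective 1 figure does not.

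**The case against.** The arithmetic is not in dispute. The case on the other side is that it hardly matters.

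- **The sample is fixed.** The comparison uses every registered pregnancy in two three-year windows, so the MDD did not set the sample size. Correcting it changes no endpoint, model or decision rule. This stands.
- **Power for the planned effect is ample.** On the stated numbers it is about 94% for a 1.5-point rise, 99.6% for 2 points and above 99.99% for the 3 points first planned for. The document does not say that 0.8 to 1.2 points is clinically meaningful. This also stands, and it means the design is not undermined. It does not rescue the claim about any clinically meaningful difference, because the protocol draws that claim directly from the wrong 0.8.
- **The analysis reports confidence intervals.** The odds ratio will come with a 95% CI, which will show what the data exclude whatever MDD was printed. This is fair and limits the harm for a careful reader. It does not make the power statement true.
- **The source of the error is not documented.** Dropping the power term gives 0.8. So does a one-sample formula that ignores sampling error in one period (0.79 to 0.82), and so does using the combined 15,857 as the size of each group (0.82 up, 0.78 down). The omitted power term is therefore only one possible explanation. All three contradict the method the protocol states, and the conclusion does not depend on which one occurred.

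**Conclusion.** The concern holds. On the protocol's own inputs the 80%-power MDD is 1.18 points for an increase and 1.09 for a decrease. Power at 0.8 points is 48.6% and 52.6% respectively, against the 80% stated. The result rests on the stated group sizes and baseline, independent births and an unadjusted two-sample comparison. Clustering by clinic and the covariates in the planned logistic model are not part of the stated calculation and were not considered here. The statement is wrong as written for a primary objective, but its practical effect is limited because the design remains well powered for the 3-point rise first planned for.

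**What to change.** In the Statistical Power section under Objective 1, restate the MDD at 80% power as about 1.2 percentage points for an increase and 1.1 for a decrease, and add that power for a 0.8-point change is about 50%. Remove the claim of sensitivity to any clinically meaningful difference, or replace it with a statement tied to a named effect, such as power above 99% for the 3-point rise in the Sample Size Calculation section.

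The cost is a short text correction and a less favourable stated sensitivity. No data, sample or analysis changes. The protocol places Objective 1 data collection in 2025-2026 with results compiled in 2026, so by that timetable the correction can be made before results are reported.
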